### Procedure

#### Recruitment

Participants will be recruited in various ways, e.g. through NGOs, general practitioners, municipalities, Polish churches, Polish supermarkets, and social media (e.g. Facebook, Instagram). To avoid potential coercion, people interested in participating in the project are invited to reach out to the research team themselves (i.e. by e-mail, telephone, or through social media). Once they reached out, the research team contacts all potential participants by phone. If they are interested, both a digital and paper informed consent form (ICF) will be sent. Permission to record DWM phone calls and/or PM + sessions for fidelity checks and digital marker analysis, and/or to provide a hair sample (see other measures), are all optional.

Once the participant has given informed consent, an online screening session is scheduled. All participants that indicate on the ICF that they are willing to give a hair sample will receive a hair sample kit consisting of instructions on how to take the hair sample, a (paper) hair questionnaire, and a prepaid envelope to return it.

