Video records of PM + sessions will be analysed for digital markers of facial activity (e.g. happiness, sadness, and fear), voice (e.g. speech prevalence), and movement (e.g. head pitch). This will be done using open-source tools based on the analysis by Galatzer-Levy et al. [74].

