### Stepped-care programme

Participants in the intervention group are offered a stepped-care programme. All participants are offered step 1. Participants who still report elevated levels of psychological distress after step 1 (i.e. score > 15.9 on the K10 at *t*_2_) are also offered step 2.

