#### *Step 2: Problem Management Plus (PM* +*)*

PM + teaches four strategies: (1) stress management, (2) problem solving, (3) behavioural activation, and (4) strengthening social support, and has a psycho-education component [27]. PM + is delivered over five weekly sessions with a non-specialist (lay) helper *(see ‘*Helpers*’)*. For this project, PM + has been adapted to be delivered in individual 60 (instead of 90) minute video-call sessions (MS Teams). Before implementation of the stepped-care interventions, a qualitative sub-study is performed to assess the main daily-life problems and psychosocial care needs of IMWs in the Netherlands, to contextually adapt both interventions [76]. Data collected for this qualitative assessment is conducted following Module 1 of the Design, Implementation, Monitoring and Evaluation (DIME) research model, which consists of free listing interviews, key-informant interviews with both IMWs and professionals and a focus group discussion [77]. Core elements of the interventions remained the same, while case examples and pictures were adapted. Details of this adaptation process will be published elsewhere.

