#### Quantitative data (RCT)

Intention-to-treat (ITT) and per-protocol (PP) analysis will be conducted for both the primary and secondary outcomes. ITT analysis will include all randomized participants (*N* = 212). PP analysis will include participants in the intervention group only if they have (a) clicked through at least three (out of five) modules of the DWM web application, and (b), if they qualified for PM + in terms of K10-distress score at *t*_2,_ attended at least four (out of five) PM + sessions. ITT analysis of the primary outcome will be used to answer the main research question.

To compare differences between the two treatment groups at baseline, t-tests (continuous variables) and chi-squared tests (categorical variables) will be conducted for normally distributed data. For continuous non-normally distributed data, Mann–Whitney tests will be conducted.

To estimate the treatment effect on the primary outcome at *t*_2_, *t*_3_, and *t*_4_, with *t*_4_ being our primary time point of interest, a linear mixed model will be used. This model will have time and treatment as fixed effects (as well as their interaction parameters), a baseline measure of the PHQ-ADS as a covariate, and subjects as random effects. The mean difference between the two treatment groups at each assessment with a 95% confidence interval will be obtained from this mixed model. The same linear mixed model will be used to estimate the effect of the DWM/PM + stepped-care programme on secondary outcomes: symptoms of depression (PHQ-9), anxiety (GAD-7), PTSD (PCL-5), quality of life (EQ-5D-5L), and an outcome-based resilience variable, operationalised as the PHQ-ADS total score against stressor exposure [78].

Missing data will not be imputed but will be treated as missing at random (MAR) as linear mixed models can handle missing data. If some items of a particular scale are missing (i.e. < 50%), the Corrected Item Mean Substitution method will be used [79]. This method uses the item mean across participants of the same study group and time point, weighted by the subject’s mean of completed items. All the above-mentioned analyses will be performed using Jamovi version 2.3.26 [80]. Jamovi is an open-source graphical user interface for R.

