As an exploratory additional analysis, digital markers will be assessed using open-source tools in a Python environment, which is available on GitHub [38, 74]. Digital markers will be assessed using open source tools in a Python environment, which is available on GitHub [38, 74]. Change over time in digital markers will be calculated using repeated measures analysis of variance (ANOVA). A covariate mixed model of the primary endpoint will be conducted by adding relevant covariates at baseline, including gender, age, education, migration and work characteristics (e.g. duration of stay, type of contract), relationship status, living situation, life events, traumatic experiences, COVID-19-related events. An exploratory analysis will also be conducted to see if steroid hormone levels and baseline and between-session change in digital markers are associated with treatment recovery.

To determine the cost-effectiveness of the DWM/PM + stepped-care programme, health economic analysis will be conducted from a healthcare system and societal perspective. This will be conducted by focusing on the incremental cost per quality-adjusted life year (QALY, based on the EQ-5D-5L) and per change in PHQ-ADS composite score at the *t*_*4*_ follow-up assessment point (week 21). To do so, the total cost of the delivery of the intervention and changes in the uptake of health care will be assessed, using the CSRI. Between-group comparison of mean costs will be conducted using appropriate statistical tests, depending on the type and distribution of data. Univariate sensitivity analysis will be conducted using non-parametric bootstrapping to estimate the uncertainty and variability on trial parameters, which will be addressed by constructing cost-effectiveness planes and acceptability curves.

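### Repeated-measures ANOVA is a poor choice for digital markers from PM+ session videos, because it discards any participant without a recording at every session analysed

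*Protocol article*

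**What the plan says.** All places are in the Protocol article.

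- **Method** (Data analysis, Quantitative data (RCT)): "Change over time in digital markers will be calculated using repeated measures analysis of variance (ANOVA"). The work is introduced with "As an exploratory additional analysis, digital markers will be assessed using open-source tools in a Python environment". A further exploratory analysis asks whether "baseline and between-session change in digital markers are associated with treatment recovery".
- **Source of the markers** (Other measures): "Video records of PM + sessions will be analysed for digital markers of facial activity", together with voice and movement.
- **Number of sessions** (Step 2: Problem Management Plus): "PM + is delivered over five weekly sessions with a non-specialist (lay) helper".
- **Who can have recordings**: step 2 is offered within the intervention group to "Participants who still report elevated levels of psychological distress after step 1" (Stepped-care programme). The Recruitment section makes consent to recording optional: "Permission to record DWM phone calls and/or PM + sessions for fidelity checks and digital marker analysis".
- **Incomplete attendance is foreseen**: the per-protocol definition accepts a stepped-up participant who "attended at least four (out of five) PM + sessions", and the Process evaluation section plans interviews with people who left during PM+.
- **Missing data** (Quantitative data (RCT)): values are not imputed and are taken as missing at random, on the ground that linear mixed models can deal with them. The one exception, item-mean substitution, concerns partly completed questionnaire scales. No rule is given for a missing recording.

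**The concern.** The article chooses a method that needs complete sets of recordings for data that it expects to be incomplete. A mixed model would use whatever sessions a participant has. Classical repeated-measures ANOVA uses a participant only if every level of the session factor is filled, so a gap must be imputed or the person removed. With imputation set aside, removal is what remains.

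Two things are at stake. The first is precision, in a group already limited to stepped-up intervention participants who agreed to be recorded. The second is selection: those with complete sets are probably the more engaged, and leaving PM+ may itself be related to outcome. Complete-case ANOVA generally needs data missing completely at random, a stronger assumption than the missing-at-random assumption adopted for the main models. If the same complete cases feed the analysis of treatment recovery, the selection carries over.

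**Working it through.** The article gives no sample size, power or recording rate for this analysis, so there is no planned figure to reproduce. The check covers how the methods behave and how large the loss could be.

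**1. Behaviour with one gap.** In simulated data for 20 participants × 5 sessions = 100 values, one value was removed. A standard repeated-measures ANOVA routine refused the data as unbalanced. Removing the affected participant leaves 19 × 5 = 95 values. A linear mixed model with session as a fixed factor and participant as a random effect ran on all 99.

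**2. Size of the loss.** Let *q* be the chance that a consenting PM+ participant has a usable recording at a given session. The values of *q* are assumptions.

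- Share with all five, sessions independent: *q*⁵.
- Limits under any dependence between sessions: lowest max(0, 1 − 5(1 − *q*)), when each gap falls on a different person; highest *q*, when all gaps fall on the same people.
- Share dropped among those with at least four recordings, sessions independent: 5*q*⁴(1 − *q*) / [5*q*⁴(1 − *q*) + *q*⁵].
- Share of planned recordings that a mixed model uses: *q*.

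| *q* | All five, independent | Possible range | Dropped among those with ≥ 4 | Used by mixed model |
|---|---|---|---|---|
| 0.95 | 0.95⁵ = 77% | 75–95% | 0.204/0.977 = 21% | 95% |
| 0.90 | 0.90⁵ = 59% | 50–90% | 0.328/0.919 = 36% | 90% |
| 0.80 | 0.80⁵ = 33% | 0–80% | 0.410/0.737 = 56% | 80% |

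**3. If only the first and last sessions are compared.** The share kept is *q*² under independence: 0.95² = 90%, 0.90² = 81%, 0.80² = 64%. The limits are max(0, 1 − 2(1 − *q*)) to *q*: 90–95%, 80–90% and 60–80%. Someone missing only a middle session stays in. Anyone who stops before the last session does not.

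**The case against.** - **The session levels are not stated.** This stands. The interest in between-session change makes a session-by-session analysis the natural reading, but does not fix five levels. A reader might infer that everyone missing one recording will certainly be deleted; the article supports this only if all five sessions enter.
- **The independence figures lean towards the pessimistic side.** This stands for the two higher rates: 77% and 59% lie near the bottom of their ranges. Missed sessions usually cluster in people who drop out, which raises the complete share and narrows the gap to a mixed model.
- **The four-of-five rule was not written for this analysis.** This stands. Per-protocol analysis is specified for the primary and secondary outcomes, and the markers are listed under Other measures. A reader might infer that the plan contradicts its own definition of adherence. It does not; the rule only shows that an adherent participant may lack a session.
- **Handling of missing recordings may be set out elsewhere.** That is possible, and the no-imputation paragraph comes before the marker paragraph, so it may not have been meant to cover markers. Neither point rescues the method, which the article names explicitly.
- **Much of the narrowing occurs under any method.** This stands. Refusal of recording and not stepping up lie outside the reach of any model. A mixed model is also not unbiased if sessions are missed for reasons tied to unobserved marker values.

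**Conclusion.** The point holds as a low-cost improvement to an exploratory analysis. The named method needs complete sets of recordings, the article foresees incomplete ones, and its only argument for leaving data unimputed applies to mixed models and not to ANOVA.

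The size is uncertain, because it rests on assumed recording rates, on the unstated session levels and on how missing sessions cluster. With five sessions it could be slight (95% complete at a rate of 0.95 with full clustering) or severe (33% at a rate of 0.80 under independence, and lower still if gaps are spread across people). The qualitative point does not depend on these rates.

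A reader might also infer that the trial's main results are affected. They are not: the primary and secondary outcomes are analysed with linear mixed models, and the health economic analysis does not use the markers.

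**What to change.** Replace the ANOVA with a linear mixed model for each marker, with session as a fixed factor, participant as a random effect and all available sessions included. State which sessions enter and report how many participants contribute at each.

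Take the between-session change for the association with recovery from this model. That use needs a participant-specific slope over session number, since a random intercept alone predicts the same change for everyone. The slope may be poorly estimated if few participants have recordings, and this should be reported if so.

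The cost is a sentence or two. No new data are needed, and the model family is already planned for the main outcomes. The article names no software for the marker ANOVA, so the package should be stated as well. The article reports 138 participants enrolled out of a planned 212 and analysis only after data collection ends, so on that timetable the change can be made before any marker data are analysed.

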#### Qualitative data (cultural adaptation and process evaluation)

Interviews and FGD will be audio-recorded and transcribed verbatim. Transcripts will be analysed thematically through inductive coding using ATLAS.ti 23.1.2.

### Data management

All data is fully accessible to the VU research team. The management of data varies per study phase.

#### Quantitative data (RCT)

Data collected through Castor EDC is automatically pseudonymised. Data is fully accessible to the VU research team. Participants give separate permission for their data (a) to be shared with partners in the RESPOND project, and (b) to be stored at the research location for 15 years, so it can be used for future scientific research into the health of IMWs. Audio and video recordings of DWM support calls and PM + sessions respectively are stored pseudonymously in an active but secured data folder in Surfdrive (i.e., a cloud service for Dutch education and research) that can only be accessed by the members of the research team. At the end of the trial, when all hair samples are collected, they will be sent to the laboratory for analysis. Participants who submitted a hair sample will be informed of the analysis results of their sample. Participants can withdraw their consent to use their information at any time. Already collected data can still be used. Collected hair samples and recordings of DWM support calls and PM + video sessions that have not yet been analysed will be destroyed.

## Qualitative data (cultural adaptation and process evaluation)

Audio recordings of interviews and FGD will be destroyed after transcription. Pseudonymised transcripts will be stored for 10 or 15 years for respectively the cultural adaptation or the process evaluation. For the process evaluation, participants must separately give permission for the use of these stored transcripts in future scientific research into the health of migrant workers.

## Trial monitoring and adverse events reporting

The project has an Ethics and Data Advisory Board (EDAB), that will monitor and advise on data management, and ethical, legal, and societal issues that arise within the project.

(Serious) adverse events ((S)AEs) are defined as any undesirable experience occurring to a participant during the study, regardless of its connection to the study procedure or the DWM/PM + intervention. All SAEs will be recorded in Castor EDC and reported to the EDAB and the Medical Ethics Committee of the Amsterdam University Medical Center (UMC), location VU University Medical Center (VUmc). The research team will follow up with all SAEs until they are stabilized or have abated. If necessary, participants will be referred to a general practitioner.

Participants can withdraw from the study at any time. No withdrawal criteria have been stated. Based on reported (S)AEs, the principal investigator (PI) can decide to discontinue participation in the trial.

## Discussion

This article presents the study protocol for an RCT in which we aim to evaluate the (cost-) effectiveness of the remotely delivered, stepped-care DWM/PM + intervention among Polish migrant workers living in the Netherlands who have elevated levels of distress. This study is part of the larger EU H2020 RESPOND project, in which three other RCTs in Western Europe will also be conducted to test the effectiveness of this intervention amongst two other migrant populations (Italy [81], France as well as health care workers (Spain) [26].

As a result of the COVID-19 pandemic, the need for psychological interventions that target the most prevalent mental health problems has increased, particularly for vulnerable groups such as IMWs. In the Netherlands, IMWs experience multiple barriers to (mental) health care [82]. To our knowledge, this is the first RCT that combines two scalable, psychosocial WHO interventions into a stepped-care programme for IMWs. As it is offered as a stepped-care intervention, as IMWs may save time and money on mental health care this as the first step may be sufficient in improving mental health. By offering this stepped-care intervention in a remote format and in IMW’s native language, mental health care may become more accessible to a population facing practical challenges in seeing a mental health care professional in the country they are residing in. Additionally, as IMWs relocate regularly (both nationally and internationally), a remotely delivered intervention allows for continuous care. If proven to be effective, this offers the possibility for upscaling and implementing the DWM/PM + programme across European health care systems for IMWs and thereby bridging the treatment gap this population faces.

## Data Availability

Data sharing does not apply to this article as no datasets were generated or analysed during the current study.

## Abbreviations

ACT: Acceptance and commitment therapy
AE: Adverse event
BTQ: Brief Trauma Questionnaire
CAU: Care-as-usual
CBT: Cognitive behaviour therapy
CSRI: Client Service Receipt Inventory
DHEA(S): Dehydroepiandrosterone (sulphate)
DIME: Design, Implementation, Monitoring and Evaluation
DWM: Doing What Matters in times of stress
eCAU: Enhanced care-as-usual (in this study PFA + CAU)
EDC: Electronic Data Capture
EQ-5D-5L: EuroQol 5-dimensional descriptive system—5-level version
GAD-7: Generalized Anxiety Disorder, seven-item measurement instrument
HCC: Hair cortisol concentrations
ICF: Informed consent form
IMW: International migrant worker
ITT: Intention-to-treat
K10: Kessler Psychological Distress Scale, 10-item measurement instrument
MAR: Missing at random
MIMIS: Mainz Inventory of Microstressors
PASS-content: Positive Appraisal Style Scale – content focused
PCL-5: PTSD Checklist for DSM-5, eight-item measurement instrument
PCL-C: PTSD Checklist for DSM-5, 20-item measurement instrument
PFA: Psychological First Aid
PHQ-9: Patient Health Questionnaire depression module, 9-item measurement instrument
PI: Principal investigator
PM +: Problem Management Plus
PP: Per-protocol
PTSD: Posttraumatic stress disorder
QALY: Quality-adjusted life year
RCT: Randomised controlled trial
SH +: Self Help Plus
ToH: Training of helpers
ToT: Training of trainers
UMC: University Medical Center
VUmc: VU University Medical Center
WHO: World Health Organization
